### Covariant

The main purpose of this study is to determine the incidence of MINS in frail patients. We will include the following baseline covariates to describe the study population and carry out Cox proportional hazard model analysis. The dependent variable is the incidence of MINS within 30 days after noncardiac surgery (using event occurrence time analysis), and the independent variable includes 24 preoperative variables (Supplemental Appendix 5).

### Informed consent

The researchers will obtain consent from the patients before surgery. For patients who cannot provide consent before surgery (such as emergency cases), researchers will obtain consent within 24 h after surgery. Eighteen centres use deferred consent procedures for patients who cannot provide consent (for example, patients taking sedatives and those undergoing mechanical ventilation) and patients who do not have close relatives available [31].

### Sampling

To reflect the seasonal, weekly and daily distributions of the number of surgical cases, patients will be randomly selected according to the methods in the previous study. Each centre is numbered from 0 to 18 in turn, and a computer will be used to generate a series of random numbers. The mantissa corresponds to each centre. At each centre, data will be collected every week or every day. Recruitment should meet two conditions: (1) Patients should be recruited from at least 1–2 centres every day during the study period. (2) For centres with a sample size greater than 20, the interval between two sampling days should be at least 15 days.

### Data management

At each subcentre, investigators will review and approved all the data. The researchers in the participating centres will directly submit the case report forms and supporting documents to the data management system (coordination centre: the First Affiliated Hospital of Shandong First Medical University). The data monitoring of this multicentre study will include a central data consistency check, statistical monitoring and on-site monitoring at all centres.

### Statistical analysis

Continuous variables will be expressed as the mean (standard deviation) or median (minimum, maximum; or interquartile interval). The classification variable will be expressed as the number of patients (percentage).A two-sided test will be used for all statistical analyses, and a difference will be statistically significant if the *P* value is less than 0.05.The chi-square test will be used to compare the overall case dropout rate between the two groups.The comparison of baseline numerical variables (such as age) between the groups will be conducted using independent sample t tests or Wilcoxon rank sum tests. Categorical variables (such as sex and the presence of comorbidities) will be compared between the groups by the chi-square test or Fisher’s exact test;The incidence of MINS within 3 days after the operation will be compared using the chi-square test.The incidences of postoperative complications and 30-day mortality will be compared with the chi-square test. The postoperative 30-day survival rate will be calculated by a survival analysis K‒M curve, and the difference between the groups will be evaluated by the log rank test.To determine the postoperative risk of MINS, multivariate logistic regression analysis will be conducted between the baseline and perioperative variables of different groups and the intervention factors, and odds ratios (ORs) and 95% confidence intervals (CIs) will be calculated. According to the main results (the occurrence or absence of MINS), the potential confounding effects on the main results will be adjusted in turn.Survival analysis of the incidence of postoperative MINS in the two groups: K‒M survival curve, Log RANK group comparison, and Cox risk proportion model.

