**Methods and analysis:**

This prospective, multicentre, real-world observational cohort study will be conducted at 18 designated centres in China from January 2023 to December 2024, with an anticipated sample size of 856 patients aged 65 years and older who are scheduled to undergo noncardiac surgery. The primary outcome will be the incidence of MINS. MINS is defined as a fourth-generation plasma cardiac troponin T (cTnT) concentration ≥ 0.03 ng/mL exhibited at least once within 30 days after surgery, with or without symptoms of myocardial ischaemia. All data will be collected via electronic data acquisition.

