#### Outcomes

**Primary outcome**

Incidence of MINS. MINS is defined as a peak plasma cTnT concentration of 0.03 ng/mL or greater that is judged to be secondary to myocardial ischaemia (i.e., no evidence of a nonischaemic aetiology causing cTnT elevation, such as sepsis, pulmonary embolism, or myocarditis), which occurs during or within 30 days after surgery. Competent physicians should be informed to further check for ischaemic symptoms, such as myocardial ischaemic symptoms and ECG changes (Supplemental Appendix 1) [13, 30]. Blood samples will be collected before surgery and on the 1st, 2nd and 3rd days after the operation. If a patient has ischaemic symptoms within 30 days after surgery, the researchers will collect blood samples again (Table 2).

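### The primary outcome is MINS within 30 days, but the plan's only comparison of MINS proportions uses 3 days, and nothing says which window carries the main result

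*Protocol article*

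**What the plan says.** The 30-day window is stated consistently where the outcome is defined. The abstract requires a raised troponin "exhibited at least once within 30 days after surgery". The Primary outcome section describes MINS as an event "which occurs during or within 30 days after surgery". The diagnostic criteria under Study implementation give the same period.

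The analyses of MINS do not all follow it:

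- Statistical analysis, test of proportions: "The incidence of MINS within 3 days after the operation will be compared using the chi-square test".
- Statistical analysis, adjusted model: "To determine the postoperative risk of MINS, multivariate logistic regression analysis will be conducted", with no window.
- Statistical analysis, time to event: "Survival analysis of the incidence of postoperative MINS in the two groups", by Kaplan-Meier curve, log-rank test and Cox model, with no window in that line.
- Covariant section: "The dependent variable is the incidence of MINS within 30 days after noncardiac surgery (using event occurrence time analysis".

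On ascertainment, the Primary outcome section says "Blood samples will be collected before surgery and on the 1st, 2nd and 3rd days after the operation", and then "If a patient has ischaemic symptoms within 30 days after surgery, the researchers will collect blood samples again".

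The Sample size calculation section compares MINS rates of 15% (frail) and 5% (non-frail) and attaches no period to them.

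**The concern.** An outcome declared over 30 days and a test of the same outcome over 3 days are two different endpoints. The article neither reconciles them nor calls the 3-day version secondary. Because the study is sized as a comparison of two proportions, a reader looking for the analysis that goes with that calculation arrives at the 3-day chi-square test. The reader cannot tell which endpoint was powered.

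The two windows also differ in how events are found. Through day 3 troponin is measured on a schedule in every patient. From day 4 to day 30 it is measured only when symptoms prompt it, and the Discussion itself warns that perioperative patients may have no ischaemic symptoms, so that MINS goes unrecognised. A 3-day count therefore reflects systematic surveillance, and a 30-day count adds symptom-triggered detections. With both windows in the plan and no ranking, the headline result could be chosen after the data are seen.

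**Working it through.** **1. Windows side by side**

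| Place in the protocol article | Window for MINS |
|---|---|
| Abstract; diagnostic criteria; Primary outcome | 30 days |
| Sample size calculation (15% v 5%) | none stated |
| Chi-square test | 3 days |
| Log-rank and Cox, Statistical analysis | none stated |
| Cox model, Covariant | 30 days |
| Logistic regression | none stated |

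One line conflicts with the outcome definition, one analysis agrees with it, and the others are silent.

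**2. Which type of test the sample size matches**

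Inputs from Sample size calculation: p1 = 0.15, p2 = 0.05, two-sided α = 0.05, allocation 570:114 = 5:1, loss 20%. The text speaks of a 90% confidence interval. I take this as 90% power, which the reproduction supports.

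- Pooled rate: (0.15 + 5 × 0.05)/6 = 0.0667.
- Uncorrected frail-group size: n = [1.960 × √(1.2 × 0.0667 × 0.9333) + 1.282 × √(0.15 × 0.85 + 0.05 × 0.95/5)]² / 0.10² = (0.5356 + 0.4743)² / 0.01 = 101.99.
- With continuity correction: (n/4) × [1 + √(1 + 2 × 6/(n × 5 × 0.10))]² = 113.68, rounded up to 114; non-frail 5 × 114 = 570.
- For 20% loss: 114/0.8 = 142.5, so 143; 570/0.8 = 712.5, so 713; total 856.

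The stated figures reproduce exactly. The calculation is a comparison of two proportions, and the only such comparison of MINS in the analysis section is the 3-day test.

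**3. What the shorter window costs in power**

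Expected events at the planned evaluable numbers: 570 × 0.05 + 114 × 0.15 = 28.5 + 17.1 = 45.6.

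Power of the uncorrected test is Φ{[(p1 − p2) − 1.960 × s0]/s1}, where s0 is the pooled and s1 the unpooled standard error. At 15% v 5%, s0 = 0.02559 and s1 = 0.03467, so (0.10 − 0.0502)/0.03467 = 1.438 and power is 92.5%.

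The article does not give the share of events after day 3. Assuming that 15% and 5% are 30-day rates and that the late share is equal in both groups:

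| Share after day 3 (assumed) | 3-day rates | Events not counted, of 45.6 | Power of 3-day test |
|---|---|---|---|
| 0% | 15% v 5% | 0 | 92.5% |
| 5% | 14.25% v 4.75% | 2.3 | 91.3% |
| 10% | 13.5% v 4.5% | 4.6 | 89.9% |
| 20% | 12% v 4% | 9.1 | 86.5% |

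If 15% and 5% were meant as 3-day rates, the 3-day test keeps 92.5% and loses nothing.

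**4. Effect on the planned number**

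The calculation names no window, so attaching 30 days to its rates leaves every input as it is: 114/570 evaluable, 856 enrolled.

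**The case against.** The strongest reply is that the 30-day outcome is analysed. The Covariant section makes 30-day MINS the dependent variable of a Cox model. The Statistical analysis section plans Kaplan-Meier curves, a log-rank test and a Cox model of MINS in the two groups, and a logistic regression on whether MINS occurred. A reader might infer that the declared primary outcome is never tested, or that the 3-day test is the only unadjusted test of MINS. Neither inference is supported: the Cox model has the declared window, and the log-rank test is an unadjusted two-group comparison that is not restricted to 3 days. A reader might also call the chi-square test the stated primary comparison. The article labels no analysis primary, so that status is only inferred from the sample-size method. Ranking of analyses is commonly left to a statistical analysis plan, so its absence here is not itself the defect.

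Two further points stand. Table 2 marks MINS at day 30, but the row is an outcome assessment, not a troponin draw, and can be read as the close of ascertainment; a footnote there would be editorial. And nothing in the documents shows that late detections differ by frailty. That is a possibility, not a finding.

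It can also be argued that the 3-day window has the cleaner ascertainment, and that a chi-square test over 30 days ignores censoring when 20% withdrawal or loss is expected. Both are fair. They are reasons to keep the 3-day result visible and to allow the 30-day log-rank or Cox analysis to be primary. They do not remove the conflict between the outcome definition and the chi-square line.

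**Conclusion.** The concern holds in this form: the one line that compares MINS proportions uses a window different from that of the declared primary outcome, and nothing in the article reconciles them. This is a conflict in stated text, not a detail left to a fuller document. It leaves open which endpoint the 15% and 5% describe and which result is the main one.

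The statistical loss is modest: about 91% to 87% power instead of 92.5%. This assumes 30-day rates, a late share of 5% to 20%, and an equal share in both groups. None of these is given in the article. Since scheduled sampling ends on day 3, the two counts can differ only through later, symptom-triggered detections, and their number is unknown. The weight of the point lies in an ambiguous primary endpoint with unequal ascertainment across the two windows, not in lost power.

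**What to change.** - Name one primary between-group analysis of MINS with the declared window, during or within 30 days after surgery. Either change the chi-square line to 30 days, or name the log-rank or Cox analysis, with its 30-day window stated, as primary.
- In Sample size calculation, state the same window for the 15% and 5% rates. If the log-rank or Cox analysis is chosen, say that the two-proportion calculation serves as its approximation.
- State the window in the logistic regression and survival lines.
- Keep MINS through day 3 as a pre-specified sensitivity analysis, labelled as the only window with scheduled troponin sampling in everyone.
- Optionally, footnote the day-30 MINS mark in Table 2 to say that blood is resampled after day 3 only if symptoms occur.

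The cost is a few sentences and one extra analysis of data already being collected. Planned enrolment and the sampling schedule stay as they are. The choice should be fixed before the data are analysed.

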## Introduction

The ageing population is quickly increasing worldwide, with the number of people aged 65 years and older expected to reach 2 billion by 2050 [1, 2]. The number of geriatric people undergoing surgery over the past 20 years has increased faster than the ageing of the population [3], which has profound implications for the planning and delivery of health and social care. Clinical frailty is the most troubling manifestation of ageing; it is described as a state of increased vulnerability to poor resolution of homeostasis after a stressful event and is the result of a cumulative decline in multiple physiological systems over a lifetime [1, 2]. Many studies have described the prevalence of frailty, and different surgical specialties have different prevalences of frailty. In patients receiving elective orthopaedic surgery, the prevalence of frailty was 23%, whereas in patients undergoing emergency hip fracture surgery, it was 53% [4, 5]. Taking cancer surgery into account, studies have reported that the prevalence of frailty is 25% in patients who undergo elective cystectomy and 39% in patients who undergo emergency general surgery, with the basal lesion usually being a tumour [6, 7]. In vascular surgery, the risk of aortic aneurysm and peripheral artery disease increases with age, and an estimated 52% of patients undergoing elective vascular surgery are frail [8]. Research on rehabilitation and related outcomes has focused on frail geriatric patients during the perioperative period. Frailty is related to adverse perioperative outcomes [9, 10].

In addition to the underlying conditions of sepsis, pulmonary embolism and arrhythmias, MINS is defined as an increase in cardiac troponin (cTn) during noncardiac surgery or within 30 days, with or without ischaemia-related symptoms and signs or myocardial ischaemic changes (with or without necrosis) [11]. Myocardial injury and infarction are considered the leading causes of death after surgery and account for 25% of all postoperative mortalities [12, 13]; ischaemic myocardial injury occurring after surgery but not meeting the criteria for myocardial infarction is more common [14, 15].

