### Eligibility criteria

#### Inclusion criteria

≥ 65 years of age;ASA grades I ∼ IV;Elective or emergency surgery;Patients undergoing noncardiac surgery;Use of general anaesthesia or regional block anaesthesia.

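### Complications, 30-day mortality and survival are compared between frail and non-frail patients by unadjusted tests only; a crude difference could partly reflect age, urgency or type of surgery

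*Protocol article*

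**What the plan says.** The Statistical analysis section of the protocol article assigns a method to each of these outcomes.

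- Complications and 30-day mortality: "The incidences of postoperative complications and 30-day mortality will be compared with the chi-square test".
- 30-day survival: "The postoperative 30-day survival rate will be calculated by a survival analysis K‒M curve, and the difference between the groups will be evaluated by the" log-rank test.
- All tests are two-sided with significance at P < 0.05.

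The adjusted analyses named in the article concern MINS.

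- Logistic model: "To determine the postoperative risk of MINS, multivariate logistic regression analysis will be conducted".
- Confounding: "According to the main results (the occurrence or absence of MINS), the potential confounding effects on the main results will be adjusted in turn".
- Time-to-event model: "Survival analysis of the incidence of postoperative MINS in the two groups: K‒M survival curve, Log RANK group comparison, and Cox risk proportion model".
- The Covariant section describes the Cox model with 24 preoperative variables in the same way: "The dependent variable is the incidence of MINS within 30 days after noncardiac surgery".

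The exposure is preoperative frailty in an observational cohort. Inclusion is open to anyone aged 65 or over, ASA I to IV, with "Elective or emergency surgery". Mortality and complications within 30 days are listed as secondary outcomes.

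**The concern.** The plan adjusts the frailty comparison for MINS, and so accepts that frail and non-frail patients differ in other ways that matter. It does not extend that adjustment to death, survival or complications, where the same differences apply. Older patients and emergency cases may well be commoner in the frail group and may also have worse 30-day outcomes whatever their frailty. A chi-square or log-rank test cannot separate these contributions.

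What is at stake is the reading of three secondary results. A significant crude difference could be taken as evidence that frailty raises the risk of death or complications when part of it comes from case mix. The Discussion makes this more likely: it concedes that the study is not randomised but still expects conclusions as convincing as those of a randomised trial.

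**Working it through.** **1. Which outcome gets which analysis**

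| Outcome | Crude comparison named | Adjusted model named |
|---|---|---|
| MINS | chi-square; Kaplan-Meier, log-rank | logistic; Cox |
| Complications | chi-square | none |
| 30-day mortality | chi-square | none |
| 30-day survival | Kaplan-Meier, log-rank | none |

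**2. Group sizes in the plan**

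The plan gives no figure for confounding, so the only figures to reproduce are the group sizes. For 15% v 5%, two-sided α 0.05, 90% power, a 5:1 ratio and continuity correction, I obtain 114 frail and 570 non-frail, as stated. Allowing for 20% loss: 114/0.8 = 142.5, rounded up to 143; 570/0.8 = 712.5, rounded up to 713; total 856. The frail share is 143/856 = 16.7%.

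**3. How far could urgency alone move a crude risk ratio?**

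Inputs from the Introduction (frailty prevalence):
- Pair A: 25% in elective cystectomy, 39% in emergency general surgery.
- Pair B: 23% in elective orthopaedic surgery, 53% in emergency hip fracture surgery.

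Assumed, because the documents do not give them: emergency share *e* = 0.15-0.40; emergency v elective risk ratio *R* = 2-6 for the outcome; no effect of frailty within urgency strata.

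Formulas, with *p*₀ the elective and *p*₁ the emergency frailty prevalence:
- overall frailty *f* = *e p*₁ + (1 − *e*) *p*₀
- emergency share among frail *a* = *e p*₁ / *f*
- emergency share among non-frail *b* = *e* (1 − *p*₁) / (1 − *f*)
- crude risk ratio = [1 + (*R* − 1)*a*] / [1 + (*R* − 1)*b*]

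Worked at *e* = 0.25, *R* = 4:
- Pair A: *f* = 0.0975 + 0.1875 = 0.285; *a* = 0.0975/0.285 = 0.342; *b* = 0.1525/0.715 = 0.213; ratio = (1 + 3 × 0.342)/(1 + 3 × 0.213) = 1.24.
- Pair B: *f* = 0.1325 + 0.1725 = 0.305; *a* = 0.1325/0.305 = 0.434; *b* = 0.1175/0.695 = 0.169; ratio = (1 + 3 × 0.434)/(1 + 3 × 0.169) = 1.53.

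Over the whole assumed range:

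| Pair | Implied overall frailty | Crude risk ratio when the true ratio is 1 |
|---|---|---|
| A (25% v 39%) | 27.1-30.6% | 1.08-1.31 |
| B (23% v 53%) | 27.5-35.0% | 1.17-1.72 |

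Both pairs imply more frailty than the plan expects (20% in its sample size section, 16.7% in its group sizes), so neither is calibrated to this cohort. Age and type of surgery are not quantified.

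**4. How much adjustment can the data carry?**

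The documents give no expected mortality. At an assumed 2%, 856 × 0.02 ≈ 17 deaths; at an assumed 5%, 856 × 0.05 ≈ 43. A mortality model can hold only a few covariates, far fewer than the 24 variables listed for the MINS model.

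**The case against.** **The aims centre on MINS.** The stated purposes are the relationship between frailty and MINS, the incidence of MINS in frail patients, and the features and 30-day outcomes of MINS in that group. A causal comparison of death or complications by frailty is not among them. This stands, and it limits the point to secondary outcomes.

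**A crude comparison is legitimate description.** This also stands. A reader might infer that the plan will report differences in age and urgency as effects of frailty. The article says only that the incidences will be compared, so misreading is a risk and not a stated intention.

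**The illustration depends on the pair chosen.** The larger range comes from setting elective orthopaedic surgery against emergency hip fracture ("In patients receiving elective orthopaedic surgery, the prevalence of frailty was 23%, whereas in patients undergoing emergency hip fracture surgery, it was 53" per cent). The same paragraph gives 52% in elective vascular surgery; against 53% for hip fracture, the same calculation yields only 1.00-1.02. The pairs mix specialty with urgency, so a reader who concludes that frailty is far commoner in emergency patients here, or that a ratio of 1.7 is to be expected, goes beyond the documents.

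**Urgency may lie on the pathway.** Frailty may itself lead to emergency surgery, for example after a fall, and adjusting for urgency could then remove part of a frailty effect. This is a fair point, and the fix allows for it.

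**The details may be in the full protocol or the SAP.** This does not dispose of the matter. The article is not silent: it names the tests for these outcomes and ties adjustment to a different one. The argument does hold for length of stay, readmission and QoR-15, for which the article names no test, so they are left out of this point.

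**Conclusion.** The point holds as a modest, inexpensive improvement to the analysis of three secondary outcomes. The article specifies crude tests at P < 0.05 for complications, 30-day mortality and 30-day survival in a non-randomised comparison, and confines adjustment to MINS. A difference found this way could partly reflect age, urgency or type of surgery.

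The size is not known. Under the assumed emergency share and emergency risk ratio, urgency alone could give a crude ratio of about 1.08-1.31 or 1.17-1.72, depending on which prevalence pair is used, and close to 1 if urgency and frailty are nearly unrelated in the cohort. These figures show that the bias is plausible; they do not forecast it. The documents do not support saying that a significant crude difference would arise without a frailty effect, only that it could. The primary MINS analysis is untouched.

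**What to change.** For 30-day mortality, 30-day survival and complications:

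1. Add a frailty estimate with a 95% confidence interval, adjusted for a short prespecified set of preoperative confounders: age and sex, plus urgency and type of surgery if these are recorded. The article names age and sex as baseline variables. Whether the other two are among the 24 covariates depends on Supplemental Appendix 5, which is not shown, and should be confirmed.
2. Use a method suited to few events, such as penalised logistic or Cox regression, or propensity weighting.
3. Show the estimate with and without urgency, because urgency may be partly a consequence of frailty.
4. Keep the chi-square and log-rank results, labelled as unadjusted and descriptive.

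The cost is a few sentences in the analysis section, a little more programming and slightly wider intervals. No extra patients or visits are needed, and no new data if urgency and type of surgery are already recorded. If the sponsor prefers not to add models, step 4 alone is the minimum.

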Frail populations often have a greater incidence of subclinical changes in cardiac structure and function, which are considered risk factors for the development of cardiovascular diseases (such as hypertension, heart failure and ischaemic heart disease) [16–19]. Many studies have focused on the development of MINS during the perioperative period, and retrospective studies involving adults aged 45 years and older are common. There is currently no pertinent research on the features, risk factors, or 30-day outcomes of MINS in frail geriatric patients. It is urgent to preoperatively assess the comprehensive health status of frail geriatric patients and to reverse or alleviate frailty as soon as possible [20]. Therefore, the main objective of this study will be to investigate the relationship between preoperative frailty and MINS in geriatric patients.

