**Secondary outcome**

b)Intraoperative haemodynamic instability and treatment times will also be recorded (Supplemental Appendix 2).c)All-cause mortality within 30 days after the operation (vascular or nonvascular; definitions are provided in Supplemental Appendix 3).d)Length of stay.e)Quality of Recovery-15 (QoR-15).f)Any complications occurred within 30 days after the operation (Supplemental Appendix 4).g)Readmission to the hospital. (Table 2)

**Table 2 Tab2:** Study assessment procedures and timetable

	STUDY PERIOD					
	Enrolment	Allocation	Postoperation			Close-out
TIMEPOINT	***-D1***	**0**	***D1***	***D2***	***D3***	***D30***
ENROLMENT						
Eligibility screen	X					
Informed consent	X					
Allocation		X				
ASSESSMENTS						
MMSE	X					
BI	X					
mFI	X					
aCCI	X					
Primary outcome						
MINS		X	X	X	X	X
Secondary outcomes						
QoR-15			X	X	X	
Postoperative complications			X	X	X	X
30-day all-cause mortality			X	X	X	X
30-day readmission			X	X	X	X

MMSE, Mini-Mental State Examination; BI, Barthel Index; mFI, modified frailty index; aCCI, age-adjusted Charlson Comorbidity Index; QoR-15, Quality of Recovery-15.

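### The logistic model for MINS mixes baseline and perioperative variables as confounder control, so if post-exposure variables enter, its frailty odds ratio is not the total effect of preoperative frailty

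*Protocol article*

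**What the plan says.** The exposure is preoperative frailty. The Introduction gives the aim: "the main objective of this study will be to investigate the relationship between preoperative frailty and MINS in geriatric patients". The Covariant section words it descriptively: "The main purpose of this study is to determine the incidence of MINS in frail patients".

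For the adjusted analysis of MINS, the Statistical analysis section opens with the purpose "To determine the postoperative risk of MINS" and states that "multivariate logistic regression analysis will be conducted between the baseline and perioperative variables of different groups and the intervention factors", with ORs and 95% confidence intervals. It then adds that "the potential confounding effects on the main results will be adjusted in turn".

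Three other places bear on this:

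- **Secondary outcome** includes "Intraoperative haemodynamic instability and treatment times will also be recorded (Supplemental Appendix 2".
- **Covariant** describes the Cox model for MINS, in which "the independent variable includes 24 preoperative variables".
- **Statistical analysis** also plans a chi-square test of MINS within 3 days, and Kaplan-Meier curves with a log-rank test and a Cox model for MINS in the two groups.

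**The concern.** Adjustment is meant to remove differences that precede the exposure and also affect the outcome. A variable that frailty itself changes during surgery is not a confounder. Holding it constant removes whatever part of the frailty effect runs through it. If an unmeasured factor drives both that variable and MINS, conditioning on it can also open a new path of bias.

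The article itself makes this more than a theoretical worry. The Introduction describes frailty as vulnerability in recovering balance after a stressor. The Discussion says that frailty affects how patients respond to and tolerate drugs and surgery. Haemodynamic instability during the operation therefore plausibly lies between frailty and MINS, and the article classes it as an outcome.

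The chi-square and log-rank comparisons are unadjusted, so in this observational cohort the logistic and Cox models supply the only adjusted estimates. Their stated covariate sets differ, and nothing says which one carries the conclusion about frailty. A reader could take a smaller logistic OR to mean that frailty had been explained away, when the model had only conditioned on part of its mechanism. The logistic sentence also refers to intervention factors, which a cohort study does not have, and it does not name frailty.

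**Working it through.** **1. The plan's own figure.** Inputs from Sample size calculation: MINS 15% in frail and 5% in non-frail patients, two-sided alpha 0.05, and 90% (called a confidence interval there, but it works numerically as power). The stated group sizes imply a ratio of 570/114 = 5. The two-proportion formula with continuity correction gives 114 frail and 570 non-frail, an exact match. Dividing by 1 − 0.20 gives 143 and 713, total 856. No stated figure is wrong.

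**2. Crude OR.** (0.15/0.85) / (0.05/0.95) = 0.1765/0.0526 = 3.35, log-OR 1.210. At 114 and 570 evaluable patients, SE = √[1/(114 × 0.15 × 0.85) + 1/(570 × 0.05 × 0.95)] = 0.325. Wald power is Φ(1.210/0.325 − 1.96) = 0.96.

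**3. OR after adjusting for one binary perioperative variable M.** Let a₁ and a₀ be the prevalence of M in frail and non-frail patients, and θ its OR for MINS within each group. For each group, solve for the intercept b that keeps the overall MINS rate at the plan's value:

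(1 − a)·expit(b) + a·expit(b + ln θ) = 0.15 (frail) or 0.05 (non-frail).

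The adjusted frailty OR is exp(b₁ − b₀). Its SE comes from the expected information of the model with frailty and M. All values of a₁, a₀ and θ are assumptions.

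Worked case, a₁ = 50%, a₀ = 25%, θ = 3:

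- Non-frail risks are 0.0344 without M and 0.0967 with M; check 0.75 × 0.0344 + 0.25 × 0.0967 = 0.050.
- Frail risks are 0.0841 and 0.2159; check 0.5 × 0.0841 + 0.5 × 0.2159 = 0.150.
- Adjusted log-OR is 0.945, so the OR is 2.57; 1 − 0.945/1.210 = 22% of the log-OR is lost.
- SE is 0.337 and power Φ(0.945/0.337 − 1.96) = 0.80.

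| M in frail v non-frail | θ | Adjusted frailty OR | Log-OR lost | Wald power |
|---|---|---|---|---|
| 40% v 25% | 2 | 3.03 | 8% | 0.92 |
| 50% v 25% | 3 | 2.57 | 22% | 0.80 |
| 70% v 30% | 4 | 2.07 | 40% | 0.56 |

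A second grid gives the same picture: 50% v 30% with θ from 2 to 5 gives 2.94 to 2.56, and 60% v 30% gives 2.75 to 2.21.

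**4. Is the direction fixed?** No.

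- M less common in frail patients (30% v 50%), θ = 2, 3, 5: adjusted OR 3.92, 4.34, 4.97.
- M unrelated to frailty (30% v 30%), θ = 2 to 5: 3.39 to 3.60. This small rise arises because an OR changes when any predictor of the outcome is added.
- Adding an unmeasured common cause of M and MINS, in five assumed settings: 2.59 to 3.68.

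**5. The two adjusted models side by side.** The Cox model has preoperative covariates only. The logistic model has baseline and perioperative variables. Once a consequence of frailty is entered in the second, the two no longer target the same effect, and a difference between them need not reflect anything in the data.

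**The case against.** The strongest reply is that the article never lists the perioperative variables. Nothing says that haemodynamic instability enters the logistic model; it is only said to be recorded. The word can equally cover type and urgency of surgery or anaesthesia, some of which are proper confounders. This stands, and it is why the point is conditional on what is entered. It does not remove the point, because the stated rule admits perioperative variables without limit and calls the adjustment confounder control.

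A second reply is that the model may be a risk-factor model. Its stated purpose is the risk of MINS, and the abstract names predictive factors as an aim; perioperative predictors are legitimate there. This also stands, but it supports keeping a prediction model under its own label. The sentence on confounding effects shows that the same model is meant to do both jobs.

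A third reply is that adjusting in turn may mean sequential adjustment, so that an estimate before perioperative variables would also be shown. The text does not settle this.

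Two stronger readings are tempting. A reader might infer that the frailty OR is certain to be biased towards no effect. Step 4 shows that it can move either way. A reader might also infer that the plan fails its main objective. It does not: the chi-square, log-rank and preoperative-covariate Cox analyses all compare MINS between frail and non-frail patients, and the two-proportion sample size is unaffected.

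**Conclusion.** The point holds as a defect in one stated covariate rule. If variables arising after the exposure are entered, the logistic frailty OR is over-adjusted, cannot be read as the total effect of preoperative frailty, and need not match the Cox result.

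For a harmful mediator more common in frail patients, which is the direction the article's own account of frailty suggests, the OR falls from 3.35 to about 2.1 to 3.0, and Wald power for that coefficient falls from 0.96 to between 0.56 and 0.92. These sizes rest on a single binary mediator with assumed prevalences and ORs, and on the plan's 15% and 5% rates; they are illustrations, not predictions. Attenuation is probable but not guaranteed. The problem is confined to this one OR and is cheap to correct.

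**What to change.** In Statistical analysis:

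1. Estimate the frailty OR for MINS from one logistic model containing frailty group and confounders fixed before incision: the preoperative set referred to in the Covariant section, with type and urgency of surgery.
2. Use the same confounder set in the Cox model.
3. Put intraoperative and postoperative variables (haemodynamic instability, its treatments, complications) in a separate model labelled as prediction or mediation, and state that its frailty coefficient is not reported as the effect of frailty.
4. Replace the reference to intervention factors with frailty group.

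This changes wording only. It needs no new data and leaves the sample size as it is. The downside is one additional secondary model to report.
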